## Data sources

### Community mapping for the endline survey

At the endline survey, prior to conducting the community census, the survey staff visited each catchment area to collect coordinates of the catchment area boundaries, as these had not been previously captured. The Zimbabwe Census office identified which EAs lay within each catchment area boundary. EAs are selected for inclusion in the survey using the sampling fraction outlined above. In the EAs selected for inclusion, all households are visited and the following screening information is collected from all mothers/caregivers within each household: name, birthdate, whether they are pregnant, if they have any children born in the past 3 years, if they have any children born in the past 3 years that were stillborn or are no longer alive. If mothers/caregivers have a child born in the past 3 years (alive or deceased), the name and birthdate of each child are recorded. Staff will utilize GPS coordinates collected from all households to revisit eligible households at designated dates and times to inform participants that they are selected and therefore invited to participate in the study.

### Endline survey of mothers/caregivers and their babies

Participating mothers/caregivers in both the 9–18 months and 19–36 month postpartum samples are asked to answer an interviewer-administered questionnaire, which captures the mother’s demographic characteristics, healthcare utilization and engagement (including changes in care location), and her experience with antenatal care, HIV testing, delivery, infant feeding, ART and PMTCT prophylaxis for the eligible child. Mothers of 19–36 month old infants who report being HIV-positive will also be asked more detailed information about engagement in HIV care after their pregnancy, their ART regimen, including reasons for any ART interruptions. Living biological mothers 9–36 months postpartum and infants 9–18 months old will be asked to provide dried blood spot samples for HIV testing. Blood spots will be air-dried onto filter papers and stored at room temperature until they are transported biweekly to the National Microbiology Reference Laboratory in Harare. Maternal samples will be tested for HIV-1 antibody using AniLabsytems EIA kit (AniLabsystems Ltd., [name]) with all positive specimens confirmed using Enzygnost Anti-HIV 1/2 Plus ELISA and discrepant results resolved by Western Blot. Among HIV-infected mothers, dried blood spot samples will be tested for HIV viral load using Biomerieux Easy Mag/Easy Q platform (Biomerieux, France).

Infant samples will be tested if the infant was born to an HIV-positive mother or if the infant was born to a mother whose sample is unavailable. Infant samples will be tested for HIV with DNA polymerase chain reaction (Roche Amplicor HIV-1 DNA Test 1.5). Mothers who participate in the study will have the option to pick up their test results from their local clinic, and will receive appropriate pre- and post- test counseling for her and her infant’s HIV test results from nurses at each health facility.

### Facility survey

In addition to the community-survey of mother infant pairs, surveyors will administer a questionnaire to the head nurse at each of the 157 health facilities in the selected catchment areas to assess the nature and integration of PMTCT and ART services offered at each facility and to collect information on other health facility characteristics. The survey also includes comprehensive resource utilization and cost information including: 1) the number and type of staff working in PMTCT, 2) PMTCT-related supplies used, 3) the monthly number of ANC and PMTCT clients in the previous calendar year, 4) the amount of staff time allocated to PMTCT services, and 5) the management practices implemented at the facility, such as supervision incentives. Facility records, such as staff rosters, supply stock records, and patient records will be used to corroborate self-reported information when available.

### Study measures

The study will estimate two primary outcomes among 9–18 month mother-infant pairs:HIV-free infant survival: The proportion of infants born to HIV-infected mothers who were alive and HIV-uninfected at 9–18 months of age. The denominator (number of HIV-infected mothers) will be assessed based on either: i) laboratory-confirmed HIV test results, ii) verbal autopsy data, or iii) information recorded on maternal health cards (for deceased or unavailable mothers). To classify deaths as due to AIDS from verbal autopsy data, we will use an algorithm validated in Zimbabwe [20]. The numerator (number of living HIV-uninfected infants) will be assessed based on: i) laboratory-confirmed HIV test results, ii) information recorded on infant health cards, and iii) reports of infants’ deaths.Mother-to-child transmission of HIV (MTCT): The proportion of infants born to HIV-infected mothers who are HIV-infected at 9–18 months of age. The denominator (number of HIV-infected mothers) will be assessed as outlined above. The numerator (number of infants HIV-infected or deceased related to HIV/AIDS) will be assessed based on: i) laboratory-confirmed HIV test results, ii) verbal autopsy data (for deceased infants), and iii) information recorded on infant health cards. A Zimbabwean pediatrician will examine the infant verbal autopsy data and rate the likelihood of each infant death being HIV-related (on a 5-point scale ranging between ‘very unlikely’ and ‘very likely’) based on: gestational age at delivery, birth weight, infant age at death, symptoms indicative of common opportunistic infections in children, along with the chronicity of their illness. She will take account of factors that affect likelihood of MTCT (e.g. breastfeeding). ‘Likely’ and ‘very likely’ cases were classified as infant HIV/AIDS-related deaths.

Secondary outcomes:3)Viral suppression: The proportion of HIV-infected mothers who are virally suppressed 9–18 months postpartum. The denominator (number of HIV-infected mothers) will be assessed as outlined above. The numerator will be assessed based on laboratory viral load test results. Mothers with viral load test results indicating < 1000 copies/ml will be classified as virally suppressed.4)Postpartum engagement in care (among mothers 19–36 months postpartum): The proportion of HIV-infected mothers who were initiated on ART and who continued ART. The denominator (number of HIV-infected mothers who were initiated on ART) will be assessed using: i) laboratory-confirmed HIV test results, or ii) information recorded on maternal health cards, when available, and iii) self-reported ART status. The numerator (number of HIV-infected mothers who were initiated on ART and continued ART after 19–36 months postpartum) will be assessed based on self-reported ART status at the time of the survey. Additionally, we will calculate the average time between delivery and discontinuation of ART among those mothers who did not continue ART.5)Heterogeneity of the impact of Option B+ on HIV-free survival and MTCT by the extent of integration of PMTCT and ART services at health facilities: Impact heterogeneity of Option B+ will be assessed using community-level cross-sectional serosurvey data as well as data on health facility characteristics from the 157 catchment areas selected as PSUs. The extent of integration of PMTCT and ART services at the facility level will be measured using multiple dichotomous variables such as: whether the facility offers both antenatal and labor/delivery services, whether the facility can initiate pregnant women on ART, whether the facility can continue women on ART after a certain number of months after delivery, whether the facility can offer ART services to male partners, and whether the facility can offer ART services to infants and children. Principal component analysis will be employed to estimate the factor loadings of these variables, in order to calculate an overall integration score per facility.6)Incremental cost effectiveness of Option B+: Assessed using effectiveness data (from the community-level cross-sectional serosurveys) along with costing data (from the 157 health facilities surveys). We will estimate the incremental cost-effectiveness ratio (ICER) of option B+ with respect to option A, and the ICER of option B+ with respect to pre-option A guidelines, as the ratio of the difference in costs over the difference in annually-adjusted effectiveness (for each of the two main outcomes: HIV-free infant survival and MTCT).

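### The rule for classing infant deaths as HIV-related leaves room for maternal ART/PMTCT exposure, so the MTCT outcome can partly incorporate the intervention being compared

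*Protocol article*

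**What the plan says.** All of this is in the protocol article.

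Under Study measures, the MTCT numerator includes some infants who died: "The numerator (number of infants HIV-infected or deceased related to HIV/AIDS) will be assessed based on" laboratory results, verbal autopsy for deceased infants, and infant health cards. The verbal autopsy part rests on one person: "A Zimbabwean pediatrician will examine the infant verbal autopsy data and rate the likelihood of each infant death being HIV-related", on a five-point scale. The rating uses "gestational age at delivery, birth weight, infant age at death, symptoms indicative of common opportunistic infections in children, along with the chronicity of their illness". The text then adds: "She will take account of factors that affect likelihood of MTCT (e.g. breastfeeding". Deaths in the top two grades count: these "cases were classified as infant HIV/AIDS-related deaths".

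The other primary outcome, HIV-free survival, is built differently: "The numerator (number of living HIV-uninfected infants) will be assessed based on" test results, health cards and reports of death. Every infant death is a failure there, whatever its cause.

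The section on the endline survey says that the mother's questionnaire records "her experience with antenatal care, HIV testing, delivery, infant feeding, ART and PMTCT prophylaxis for the eligible child".

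**The concern.** For an infant who died untested, the rating stands in for a test of whether transmission occurred. A rating that draws on the clinical picture measures something about the infant. A rating that also draws on predictors of transmission imports what the rater already believes about those predictors. Where a predictor is the programme under evaluation, the outcome is no longer measured independently of exposure.

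The comparison is between survey rounds, and the rounds are defined by regimen era. Two infants with the same clinical course could be graded differently because one mother was on ART. That would move MTCT between rounds with no change in transmission. MTCT is one of two primary outcomes and one of the two effect measures in the incremental cost-effectiveness ratio.

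The Analyses section is careful on a related matter: it limits adjustment to covariates that the intervention does not affect. The outcome rule carries no such limit.

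**Working it through.** **1. Does the open list cover the regimen?** The Background gives transmission of 15 to 45% when neither ARV prophylaxis nor ART is used, and describes PMTCT effectiveness as depending on ART efficacy and on engagement in services. By the article's own account, then, maternal ART affects the likelihood of transmission. Study measures offers breastfeeding only as an example and excludes nothing. The regimen is recorded in the survey, but the article does not say whether those fields reach the rater, who works from the verbal autopsy data.

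**2. Is the regimen tied to the comparison?** Yes. The 2012 round is pre-Option A, the 2014 round is Option A, and the 2017–18 round is Option B+. Results for 2012 and 2014 are already cited under Statistical power while the last round is still to be collected. Rating round by round therefore looks likely, though the article does not say so.

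**3. Which results can it reach?**

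| Result | Uses the rating? |
|---|---|
| MTCT, living infants with a laboratory result | No |
| MTCT, untested deceased infants | Yes |
| HIV-free survival | No |
| Cost-effectiveness ratio based on MTCT | Yes, through MTCT |
| Cost-effectiveness ratio based on HIV-free survival | No |

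**4. Scale.** The article states no figure for this step, so there is none to reproduce. Inputs from Statistical power: 13,000 pairs, 2% refusal, 11.5% HIV prevalence.

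- Expected exposed infants: N = 13,000 × 0.98 × 0.115 = 1,465.
- Shift per reclassified death: 1 / 1,465 = 0.068 percentage points, unweighted.
- For 5, 10 and 15 deaths: 5/1,465 = 0.34, 10/1,465 = 0.68 and 15/1,465 = 1.02 points.

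The number of deaths among exposed infants is not given. As an assumption, let a share d of exposed infants die, and let a share s of those deaths be graded differently between rounds for the same clinical picture. The shift is d × s.

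- Low: d = 1%, s = 10%: 0.01 × 0.10 = 0.1 points (1,465 × 0.001 = about 1 infant).
- High: d = 3%, s = 50%: 0.03 × 0.50 = 1.5 points (1,465 × 0.015 = about 22 infants).

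**5. What the 2012 figures add.** They are 9% infected and 10% infected or dead, a gap of about 1 point. The gap suggests that few deaths were left outside the infected group. It does not show how many of the 9% were deaths placed there by rating.

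**The case against.** The strongest reply is that the chain from regimen to rating is inferred. The article names breastfeeding and five clinical items, never ART. The regimen fields belong to the mother's questionnaire, and nothing says that the rater sees them. This stands as a limit on certainty. It does not remove the instruction, whose plain meaning includes ART and which nothing in the section narrows.

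A reader might infer that the rule must bias MTCT in favour of Option B+. The documents do not support that. It would need the rater to know ART status, to discount deaths because of it, and to meet ART-exposed deaths more often in the last round. No ART coverage by round is given. For breastfeeding, the one factor named, no data by round are given either; longer breastfeeding in the last round could push ratings the other way.

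A reader might also treat the absence of masking as a fault in itself. In a condensed article, silence on rater procedure is not a defect; the point rests on the rule that is stated.

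Setting the shift against the planned 1.4-point difference (4.8% to 3.4%) would also mislead. That difference is for infection or death, which the rating cannot change, and the article gives no planned difference for MTCT. At 3.4% about 50 events of all kinds are expected (1,465 × 0.034), so the upper end of the assumed range would be a large share of them.

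Two further replies stand. HIV-free survival already shows the result with every infant death counted, so a rating-driven fall in MTCT should appear as divergence between the two outcomes. And breastfeeding is a real route of transmission, so using it to judge an untested death is defensible.

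**Conclusion.** The concern holds as a credible path from exposure to outcome in one of two primary outcomes, not as demonstrated bias. It is confined to untested deceased infants in MTCT and to the cost-effectiveness ratio that uses MTCT. Laboratory-tested infants and HIV-free survival are untouched.

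Each reclassified death is worth about 0.07 points at the expected sample. The range of 0.1 to 1.5 points rests on assumed death and reclassification shares, and on unweighted counts; survey weights would make some deaths count for more and others for less. The error favours Option B+ only if the rater discounts ART-exposed deaths. Otherwise its sign is open.

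**What to change.** In Study measures, close the list and state what is withheld. For example: *The rating uses only gestational age, birth weight, age at death, symptoms, chronicity of illness and infant feeding. Maternal ART and PMTCT information, infant prophylaxis, survey round and calendar dates are removed from the file before rating.*

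Have the same rater grade the 2012, 2014 and 2017–18 deaths together in random order.

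Add one sensitivity analysis in which the MTCT numerator counts only infections documented by laboratory result or health card. Report it beside 1 minus HIV-free survival. The first counts no rated death and the second counts every infant death, so the two bracket whatever the rating contributes.

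The cost is somewhat less information per rating, preparation of the stripped files, and re-rating of the earlier records, whose number the article does not give. No new data are needed, provided that the earlier verbal autopsy records are still available.

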### Study site and population

A timeline of data collection activities for the three cross-sectional serosurveys is summarized in Fig. 1. The study population consists of infants born 9–18 months prior to the surveys (alive or deceased) and their mothers or caregivers (at least 16 years old) living in the catchment areas of 157 randomly selected health facilities in five of Zimbabwe’s ten provinces. The five provinces (Harare, Mashonaland West, Mashonaland Central, Manicaland, and Matabeleland South) were selected in 2012 to include three of the four largest cities in Zimbabwe, rural communities with high and low HIV prevalence, and both major ethnic groups in Zimbabwe (i.e. Shona, Ndebele). The 2017–18 survey will include an additional sample of mothers at least 16 years old who have infants 19–36 months of age in order to examine retention in care. Caregiver-infant pairs are enrolled even if the mother of an eligible child has died or has left the baby for a prolonged period of time (e.g., working elsewhere).

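### The viral-suppression outcome borrows a denominator that includes deceased and absent mothers, who cannot have the viral load its numerator requires

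*Protocol article*

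**What the plan says.** The Study measures section defines the outcome as follows: "The proportion of HIV-infected mothers who are virally suppressed 9–18 months postpartum". It then fixes the two parts of the ratio: "The denominator (number of HIV-infected mothers) will be assessed as outlined above. The numerator will be assessed based on laboratory viral load test results". A mother counts as suppressed if she has a result "indicating < 1000 copies/ml will be classified as virally suppressed".

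The only earlier outline of the denominator is under the first primary outcome, HIV-free infant survival. There a mother is counted as HIV-infected by laboratory test or by "ii) verbal autopsy data, or iii) information recorded on maternal health cards (for deceased or unavailable mothers").

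Other sections show who these mothers are and who can be tested:
- Study site and population: "Caregiver-infant pairs are enrolled even if the mother of an eligible child has died or has left the baby" for a prolonged period.
- Endline survey of mothers/caregivers and their babies: "Living biological mothers 9–36 months postpartum and infants 9–18 months old will be asked to provide dried blood spot samples for HIV testing".
- Same section: "Among HIV-infected mothers, dried blood spot samples will be tested for HIV viral load".

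**The concern.** The wide denominator suits the infant outcomes, because an infant whose mother has died or is away can still be tested or have its death recorded. Viral suppression is a laboratory measurement on the mother herself. A mother who enters the denominator through verbal autopsy, or through a health card because she is not there, has no route into the numerator.

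The resulting percentage would be read as the share of HIV-infected mothers with controlled virus. It would in fact be that share reduced by maternal death and by absence. Unknown status would be recorded as failure for living women who happen to be elsewhere. A larger sample does not remove this, because the relative reduction depends only on the share without a result.

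**Working it through.** **Step 1: trace each route through the definition (Study measures; Endline survey section).**

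| How the mother is classified HIV-infected | In denominator? | Can have a viral load? | Effect as written |
|---|---|---|---|
| Laboratory test, valid viral load | Yes | Yes | Suppressed or not, as measured |
| Laboratory test, viral load assay fails | Yes | No result | Not in numerator |
| Verbal autopsy (deceased) | Yes | No | Not in numerator |
| Health card, deceased | Yes | No | Not in numerator |
| Health card, living but unavailable | Yes | No | Not in numerator |

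The article has no sentence that restricts the denominator to mothers with a result. It does not say how mothers without one are handled.

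**Step 2: do the weights repair it?** The Analyses section describes final-round weights for selection of clinics and enumeration areas, for incomplete census data, and for survey non-response among identified eligible pairs. A pair enrolled through a caregiver has responded. No weight is described for a missing maternal specimen.

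**Step 3: size.** The article states no expected suppression rate, sample size or power for this outcome, so there is no figure to reproduce. Let p be the proportion suppressed among tested mothers and f the share of the denominator without a result.

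- Reported proportion = p(1−f)
- Gap below the tested-mother proportion = p·f
- Expected HIV-infected mothers = 13,000 × 0.115 = 1,495 (planned pairs and assumed prevalence, Statistical power section)

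Both p and f are assumptions. At p = 80%:

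| f | Mothers without a result (1,495·f) | Reported | Gap (points) |
|---|---|---|---|
| 1% | about 15 | 79.2% | 0.8 |
| 2% | about 30 | 78.4% | 1.6 |
| 5% | about 75 | 76.0% | 4.0 |
| 10% | about 150 | 72.0% | 8.0 |

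Over p = 60–90%, the gap is 0.6–0.9 points at f = 1% and 6.0–9.0 at f = 10%. For comparison, the simple-random-sample standard error at p = 80% is √(0.8 × 0.2 / 1,495), about 1.0 point. A design effect would enlarge it.

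**Step 4: the gap is not automatically the bias.** Suppose all mothers without a result are living, and a proportion q of them are suppressed. The population value is p(1−f) + q·f. The definition as written is then too low by q·f, and an unweighted tested-only figure is too high by (p−q)·f. With p = 80% and f = 5%:

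| Assumed q | Population value | As written (76.0%) | Tested only, unweighted (80.0%) |
|---|---|---|---|
| 60% | 79.0% | 3.0 low | 1.0 high |
| 40% | 78.0% | 2.0 low | 2.0 high |
| 20% | 77.0% | 1.0 low | 3.0 high |

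Simply dropping untested mothers is therefore not a full cure. Below q = p/2 it does worse than the present rule.

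**The case against.** The best defence is that the cross-reference covers only how HIV status is ascertained. On that reading the outcome describes living women, and mothers without a viral load would be treated as missing under rules in a fuller document. The reading is possible, but the article states it nowhere. The article does not leave the denominator open; it names one, and that one does not match the numerator. The next outcome, postpartum engagement in care, has its own list of denominator sources, without verbal autopsy, so the authors did tailor a denominator where they saw the need.

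A second defence is that counting death as non-suppression can be a deliberate composite. It can, but the article does not say so, and it would not justify the same treatment of living, absent mothers.

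Several stronger readings are tempting and are not supported:
- *That comparisons of suppression between rounds or areas are distorted.* The Analyses section specifies such comparisons for MTCT and HIV-free survival only, and none for suppression.
- *That every unsampled mother counts as unsuppressed.* Health cards are specified as the source for deceased or unavailable mothers. A mother who is present but declines the blood spot is not clearly in the denominator.
- *That suppression is understated by a known amount.* The article gives neither p nor f, and p·f equals the bias only if untested living mothers are suppressed at the same rate as tested ones.
- *That suppression is understated for deceased mothers.* They have no suppression status to understate; the issue there is what the proportion is meant to describe.

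**Conclusion.** The numerator and denominator of secondary outcome 3 refer to different sets of mothers. As written, HIV-infected mothers who are deceased or absent are in effect counted as not suppressed, and the described weights do not address this. The proportion therefore blends suppression with maternal death and absence.

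The size cannot be derived from the article. For assumed f of 1–10% and p of 80%, the reported figure lies 0.8 to 8.0 points below the proportion among tested mothers. At f = 1% that is within one standard error and minor; at f = 5% or more it is several standard errors under simple random sampling. For living untested mothers, the true bias depends on their own unknown suppression rate. The point concerns one secondary outcome and leaves both primary outcomes untouched.

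**What to change.** Replace the cross-reference in secondary outcome 3 with its own definition:

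1. Denominator: living HIV-infected biological mothers 9–18 months postpartum.
2. Estimation: suppression among those with a valid viral load, using weights that also cover missing maternal specimens, including those in pairs enrolled through a caregiver.
3. Reporting: numbers of deceased, absent and otherwise untested HIV-infected mothers, by reason, separately from the proportion.
4. Bounds: living untested mothers counted as all suppressed and as all unsuppressed. In the illustration with p = 80% and f = 5%, all living, these are 0.80 × 0.95 + 0.05 = 81.0% and 0.80 × 0.95 = 76.0%.

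If a composite with death is wanted, state it and report it as a separate quantity.

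The cost is a short change to the outcome definition, one further weighting step and a small table, with no new data. The drawback is that the main estimate then relies on weighting for living mothers without a result; the bounds show how much depends on that.

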## Methods/design

### Specific objectives

The specific objectives of this study include:Objective 1a, 1b: Compare the population-level impact of Option B+ on HIV-free survival and MTCT among infants 9–18 months of age in Zimbabwe to: a) standard of care before Option A; and b) Option A.Objective 2: Use facility and community level data to assess heterogeneity of the impact of Option B+ on HIV-free survival and MTCT among infants 9–18 months of age by the extent of integration of PMTCT and ART services at health facilities, among other factors.Objective 3: Assess retention of mothers in ART services 19–36 months postpartum.Objective 4a, 4b: Determine the cost-effectiveness of Option B+ compared to: a) the standard of care before Option A; and b) Option A.

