To assess heterogeneity of the impact of Option B+ on HIV-free survival and MTCT among infants 9–18 months of age by the extent of integration of PMTCT and ART services at health facilities (Objective 2) we will first describe the variability in service integration, and characteristics of the facilities and catchment populations. We will capitalize on the variation of the integration score and other facility characteristics across the catchment areas to examine whether they affect the effectiveness of Option B+. We will describe differences in HIV-free survival by these facility-level characteristics. We will employ two identification strategies for these analyses. First, we will model 2017–18 outcomes adjusted for 2012 characteristics in each facility using ordinary least squares regression with HIV-free infant survival (or MTCT) as the aggregate continuous outcome. Similarly, we will model 2017–18 outcomes adjusted for 2014 characteristics. Second, we will apply a “difference-in-difference” approach, in which the outcomes will be defined as a) changes in HIV-free survival (or MTCT) between 2017 and 18 and 2012 in each catchment area, as well as b) changes in the same outcomes between 2017 and 18 and 2014.

Analysis for the retention of mothers in ART services after 19–36 months postpartum (Objective 3) will be primarily descriptive due to small sample size (e.g. 10% of eligible mothers 19–36 months postpartum). We will explore possible variations in the proportion of mothers who continued ART after weaning by whether the HIV-infected mother was or not on ART prior to PMTCT, to assess whether asymptomatic mothers were retained in care. We will also examine the average time between weaning and discontinuation of ART among those mothers who did not continue ART.

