Finally, the population-level benefits of Option B+ are predicated on mothers being retained in care for life, and our design will be one of the first population-based assessment of retention in HIV care up to 3 years postpartum among mothers who received Option B+. By simplifying service delivery and reducing the number of steps that mothers need to negotiate, Option B+ is expected to improve retention in care and adherence to ART. Given that the postulated benefits of Option B+ are predicated on HIV-infected mothers staying on ART beyond breastfeeding, our study design will test this assumption.

Our study is subject to limitations. Although our estimates account for transmissions occurring during the first 9–18 months of breastfeeding, HIV-exposed infants may still be breastfeeding at the time of the survey (median duration of breastfeeding is 17.8 months in Zimbabwe) [33]. Estimates of HIV-free survival for 9–18 month old infants may therefore overestimate HIV-free survival at 24 months (at the end of breastfeeding) and may result in an underestimation of MTCT. Nonetheless, estimates restricted to all HIV-exposed infants no longer breastfeeding at the time of our 2012 survey were comparable: 91.9% (95% CI: 86.8–95.1) HIV-free infant survival and 8.1% (95% CI: 4.9–13.2) MTCT [9].

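### Secondary outcome 4 is worded as continuing ART but measures ART use on the survey day, so it cannot by itself show that mothers stayed on ART beyond breastfeeding, and restarters drop out of the discontinuation summaries

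*Protocol article*

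**What the plan says.** Objective 3 (Specific objectives) is to "Assess retention of mothers in ART services 19–36 months postpartum". Study measures turns this into secondary outcome 4: "The proportion of HIV-infected mothers who were initiated on ART and who continued ART". The numerator rule reads "continued ART after 19–36 months postpartum) will be assessed based on self-reported ART status at the time of the survey".

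The companion summary in the same section is the "average time between delivery and discontinuation of ART among those mothers who did not continue ART". The Analyses section plans a similar average, counted from weaning instead of delivery and again restricted to mothers who did not continue. It also describes the share continuing after weaning according to whether the mother was on ART before PMTCT. The Objective 3 analysis "will be primarily descriptive due to small sample size".

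Under Endline survey of mothers/caregivers and their babies, mothers of 19–36 month old infants who report being HIV-positive are asked about engagement in care after pregnancy and "their ART regimen, including reasons for any ART interruptions". No stated outcome refers to those answers.

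The Discussion states that the postulated benefits of Option B+ are "predicated on HIV-infected mothers staying on ART beyond breastfeeding, our study design will test this assumption".

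**The concern.** Continuing treatment describes an interval; ART status on the interview day describes one point. A mother who stopped after weaning, was off ART for some months and restarted before the visit answers truthfully that she is on ART and is counted as having continued. The problem is therefore separate from the accuracy of self-report.

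The same rule decides who enters the discontinuation summaries. Both are limited to mothers who did not continue, so a restarter is in neither, and her stop appears in no summary that the article describes.

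At stake is the conclusion drawn in the Discussion. Of the six outcomes listed, outcome 4 is the only one that measures ART continuation in the 19–36 month sample; the viral suppression outcome is defined at 9–18 months. A high survey-day figure would be compatible with most mothers never stopping, and also with a sizeable group stopping and returning. The first supports the claim about staying on ART beyond breastfeeding; the second does not.

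**Working it through.** **1. Who is counted where.** Apply the stated rules to three mothers, all initiated on ART.

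| Mother | On ART at survey | Outcome 4 | In time to discontinuation | Stayed on without a break |
|---|---|---|---|---|
| Never stopped | yes | continued | no | yes |
| Stopped, still off | no | not continued | yes | no |
| Stopped, restarted | yes | continued | no | no |

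The third row is the problem. Every mother on ART without a break up to the survey is on ART at the survey, but not the reverse. So the survey-day share is at least the uninterrupted share, and the difference is the share who are on ART after a stop.

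**2. The plan's own figure.** Statistical power gives about 1800 pairs and about 200 HIV-infected mothers, at 11.5% prevalence; the 2% refusal rate is stated there for the 2017–18 survey. 1800 × 0.98 × 0.115 = 202.9, so the figure reproduces. The document gives no expected retention share, stop rate or restart rate, so everything below is assumed.

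**3. Size, two-state model.** Assume every mother is on ART at delivery, a constant monthly stop rate l and restart rate m, and survey times spread evenly over t = 19 to 36 months.

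- On ART at t: m/(l+m) + [l/(l+m)]·exp(−(l+m)t)
- Never stopped by t: exp(−lt)
- Mean of exp(−kt) over 19–36: [exp(−19k) − exp(−36k)]/(17k)

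For l = 0.01, m = 0.05:
- k = 0.06: (0.3198 − 0.1153)/1.02 = 0.2005. On ART = 0.8333 + 0.1667 × 0.2005 = 86.7%.
- k = 0.01: (0.8270 − 0.6977)/0.17 = 0.760. Never stopped = 76.0%.
- Gap 10.6 points, or about 21 of 200 mothers.

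The nine combinations (gaps taken before rounding):

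| Stop per month | Never stopped | Gap, restart 2% | Gap, restart 5% | Gap, restart 10% |
|---|---|---|---|---|
| 0.5% | 87.2% | 3.0 | 5.8 | 8.4 |
| 1% | 76.0% | 5.4 | 10.6 | 15.4 |
| 2% | 58.0% | 9.0 | 17.9 | 26.1 |

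With m = 0 the two formulas coincide and the gap is zero. These gaps compare survey-day use with no break since delivery. Against no break after weaning the gap is smaller, because a mother who stopped and restarted before weaning no longer counts as interrupted.

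**4. Size, without a model.** Gap = (share on ART at survey) × (share of those who had stopped and restarted). With 70–90% on ART:

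| Restarters among those on ART | Gap in points | Mothers of 200 |
|---|---|---|
| 0% | 0 | 0 |
| 5% | 3.5–4.5 | 7–9 |
| 10% | 7–9 | 14–18 |
| 20% | 14–18 | 28–36 |

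**5. Against sampling error.** The simple 95% half-width, 1.96·√(p(1−p)/200), is 6.4, 5.5 and 4.2 points at p = 0.7, 0.8 and 0.9. The true half-width will be wider: the denominator is only mothers initiated on ART, and the sample is clustered and weighted.

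**The case against.** The strongest reply is that nothing is biased. Outcome 4 is headed as engagement in care, Objective 3 speaks of retention in ART services at 19–36 months, and a cross-sectional survey measures exactly that by asking who is on ART now. A mother who lapsed and returned is arguably retained, and the numerator rule is stated openly. This stands for Objective 3. It does not rescue the word continued, the Discussion claim, or the loss of restarters' stops from the discontinuation averages.

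A second reply is that an article need not say how each questionnaire item is tabulated. That also stands: a reader might infer that the interruption answers will be ignored, but the article does not say so. The point here is narrower: the article does fix a numerator, and that numerator does not use them.

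A reader might also infer that the rule tilts the comparison in favour of Option B+. The document does not support that. The 19–36 month sample exists only in the 2017–18 round, no comparison with an earlier round is planned for it, and the analysis is primarily descriptive.

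Finally, the size is assumed throughout. The 26-point figure is the extreme corner of the grid, hazards are taken as constant, and the model starts every mother at delivery although the Analyses section recognises that some were on ART before pregnancy. All of this stands.

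**Conclusion.** The point holds as a mismatch between a stated rule and a stated conclusion. Survey-day status is a sound measure of current ART use at 19–36 months. It is mislabelled as continuation, cannot by itself test whether mothers stay on ART beyond breastfeeding, and removes mothers who stopped and restarted from both discontinuation summaries. If continuation means without a break, the direction is certain: the survey-day share equals or exceeds the uninterrupted share.

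The size is not known from the document. It is about 3 to 26 points under assumed monthly stop rates of 0.5–2% and restart rates of 2–10%, measured since delivery, and zero if nobody restarted. A flat statement that retention is overstated would go too far: it presumes both that restarting occurs and that retention means uninterrupted treatment.

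The outcome is secondary and descriptive. HIV-free survival, MTCT and the cost-effectiveness ratio do not use it. The change is still worth making, because a descriptive result rests on its definition.

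**What to change.** - **Relabel** the present measure as on ART at the time of the survey, and keep it for Objective 3.
- **Add** the proportion on ART at the survey with no interruption after weaning and, separately, with none since delivery (or since ART initiation, if later). State in advance the minimum gap that counts as an interruption. Derive both from the interruption items already in the endline questionnaire, and rest the Discussion claim on the after-weaning measure.
- **Include** mothers who stopped and restarted in time to first discontinuation, from delivery and from weaning, where the timing was recorded.
- **Fallback:** the article mentions reasons for interruptions and does not show whether dates or durations are asked. If the items record only whether an interruption occurred, report the added measure as no reported interruption, without placing it before or after weaning.

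Cost: rewording and a few derived variables, with no new data collection if timing was asked. The added measures depend on recall of past interruptions and will give a figure no higher, and probably lower, than the present one. Both limits should be reported with the result.
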